## Abstract

**Background:**

The physical wellbeing of people with mental health conditions can often be overlooked in order to treat the primary mental health condition as a priority. Exercise however, can potentially improve both the primary psychiatric condition as well as physical measures that indicate risk of other conditions such as diabetes mellitus and cardiovascular disease. Evidence supports the role of exercise as an important component of treatment for depression and anxiety, yet no randomised controlled trials (RCT's) have been conducted to evaluate the use of exercise in the treatment of people with post traumatic stress disorder (PTSD).

This RCT will investigate the effects of structured, progressive exercise on PTSD symptoms, functional ability, body composition, physical activity levels, sleep patterns and medication usage.

**Methods and design:**

Eighty participants with a Diagnostic and Statistical Manual of Mental Disorders (DSM-IV) diagnosis of PTSD will be recruited. Participants will have no contraindications to exercise and will be cognitively able to provide consent to participate in the study.

The primary outcome measures will be PTSD symptoms, measured through the PTSD Checklist Civilian (PCL-C) scale. Secondary outcome measures will assess depression and anxiety, mobility and strength, body composition, physical activity levels, sleep patterns and medication usage. All outcomes will be assessed by a health or exercise professional masked to group allocation at baseline and 12 weeks after randomisation.

The intervention will be a 12 week individualised program, primarily involving resistance exercises with the use of exercise bands. A walking component will also be incorporated. Participants will complete one supervised session per week, and will be asked to perform at least two other non-supervised exercise sessions per week. Both intervention and control groups will receive all usual non-exercise interventions including psychotherapy, pharmaceutical interventions and group therapy.

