## Methods/design

### Design

An assessor-blinded RCT will be conducted. A total of 40 participants in each group (n = 80) will be recruited. The study will have 80% power to detect as significant at the 5% level a 5 point between group difference on the PCL-C (SD = 9.4) [13] allowing 15% dropouts. The study protocol has been designed and will be reported, with reference to the CONSORT Statement [14]. Figure 1 gives an overview of the study design.

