### Randomisation

Upon admission to the hospital as either an in-patient or out-patient, a routine physical assessment will be conducted by a consulting medical officer to assess trial eligibility based on physical limitations. This initial assessment will also be used to confirm that the potential participant meets the DSM-IV diagnosis of PTSD. Eligible subjects will then be invited to participate in the trial by the research team. Posters, flyers and other marketing material will be distributed around the facility to promote awareness of the trial. Outpatients eligible to participate will be informed of the study through hospital staff at various times throughout their contact with the hospital.

Once consent has been obtained, the baseline assessment will be conducted and participants will then be randomised to either the exercise intervention or control group. Allocation to groups will be undertaken by a staff member not involved in recruitment (to ensure allocation concealment) using a block randomisation sequence generated using random numbers in Excel and including randomly varying block sizes. Participants and intervention staff are unable to be blinded to group allocation, but health and exercise professionals assessing all outcome measures will be blinded to group allocation.

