### Outcomes

#### Data Collection

Data will be collected from clinician interviews, self-report questionnaires, exercise, medication use and sleep diaries, and physical assessments. Health or exercise professionals collecting data will be blinded to group allocation. Physical assessments will be carried out at baseline, and following the 12 week intervention. All tests will be conducted in an examination room at the hospital. Assessments will take approximately 30 minutes to administer. All assessments will be carried out by an assessor blinded to group allocation.

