### Outcome measures

#### Post Traumatic Stress Disorder symptoms

The primary aim of this study is to examine the effects of individualised, structured exercise on PTSD symptoms. This will be measured using the PTSD Checklist-Civilian [21], a self-report questionnaire comprising 17 items relating to the main symptoms of PTSD. Participants are asked to indicate how much they have been bothered by a particular symptom over the past month using a 5-point (1-5) scale.

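### The blanket claim that all outcomes are assessed by masked professionals does not fit the primary PCL-C or most secondary outcomes, which are rated by participants who know their allocation

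*Protocol article*

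**What the plan says.** The Abstract (Methods and design) says: "All outcomes will be assessed by a health or exercise professional masked to group allocation at baseline and 12 weeks after randomisation". The Randomisation section says that "health and exercise professionals assessing all outcome measures will be blinded to group allocation", and Data Collection says: "All assessments will be carried out by an assessor blinded to group allocation". None of the three is limited to a type of outcome. The Design section adds the label: "An assessor-blinded RCT will be conducted".

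The Randomisation sentence that makes the masking claim also concedes: "Participants and intervention staff are unable to be blinded to group allocation". On the primary outcome the Abstract says: "The primary outcome measures will be PTSD symptoms, measured through the PTSD Checklist Civilian (PCL-C) scale". The outcome section for PTSD symptoms describes that scale as "a self-report questionnaire comprising 17 items relating to the main symptoms of PTSD", with each item rated by the participant.

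On sources, Data Collection says: "Data will be collected from clinician interviews, self-report questionnaires, exercise, medication use and sleep diaries, and physical assessments". It then states in general terms that the professionals who collect data are blinded.

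**The concern.** For a questionnaire about one's own symptoms, the respondent's judgement produces the score. If the respondent knows the allocation, masking the person who hands over, collects or scores the form leaves that judgement unblinded. A reader of the Abstract would take the primary result as obtained under masked assessment, when the judgement behind it is not masked.

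This matters more because the comparator is usual care. The article describes supervised weekly sessions, goal setting and motivational interviewing for the exercise arm and no matching contact for controls, so expectation may differ between arms. The Abstract's Discussion and the main Discussion both say that the study will determine the effect or role of exercise, without noting this limit.

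There is also an operational question. If the blinded assessor handles the exercise diaries, masking could be lost for the outcomes where it does work, including effort-dependent tests such as the 6-minute walk and knee extension.

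**Working it through.** The plan gives no figure on this point, so the check sets the masking statements against the outcome definitions.

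**Step 1: who produces each value.** The sections under Outcome measures cover seven domains.

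| Domain | Measure | Source of the recorded value |
|---|---|---|
| PTSD symptoms (primary) | PCL-C | Participant, stated as self-report |
| Depression and anxiety | DASS | Participant, stated as self-report |
| Physical activity | IPAQ short form | Participant's answers; the section does not say who fills in the form |
| Sleep | PSQI and PTSD addendum | Participant, stated as self-report |
| As-needed medication | Weekly diary, plus notes while an inpatient | Participant for the diary, hospital record for the notes |
| Mobility, fitness, strength | Balance, chair rise, 6-minute walk, grip, knee extension | Staff tester |
| Body composition | Heart rate, blood pressure, weight, height, fat percentage, circumferences | Staff measurement |

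Five of the seven domains rest wholly or partly on participant report: the primary outcome and 4 of the 6 secondary domains. Two domains (7 − 5 = 2) are measured by staff.

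**Step 2: combine with blinding status.** Participants are not blinded (Randomisation). For the five participant-reported domains, the source of the value is therefore unblinded, apart from the inpatient notes. The statements that all outcomes, all outcome measures and all assessments are masked can be true only of administration and scoring in these domains.

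**Step 3: look for a narrowing statement or a blinded rating.** No section limits the masking claim to observer-measured outcomes. Data Collection lists clinician interviews as a source, but no outcome section is tied to them, so the article describes no blinded clinician rating of PTSD symptoms.

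**Step 4: the diaries.** Data Collection names exercise diaries among the sources and then says that those collecting data are blinded. The Intervention and Motivational Tools sections describe the diaries only within the exercise programme: they hold sets, repetitions and walking, and guide progression. Pedometers go to the intervention group. The Control Group section mentions no exercise diary. On these statements, a blinded assessor who received such a diary would learn the allocation. The article does not say who receives them.

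**Step 5: size.** Seventeen items scored 1 to 5 give a range of 17 × 1 = 17 to 17 × 5 = 85. The design difference of 5 points averages 5/17 = 0.29 of a point per item. This describes the target on its scale. It says nothing about how large a reporting bias would be.

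**The case against.** The strongest reply is that nothing is hidden. The article says openly that participants are unblinded and labels the PCL-C, DASS, sleep indices and medication diary as self-report. It never claims that masking protects the PCL-C rating itself. Self-report with unblinded participants is common and defensible in exercise trials. All of this stands, but it does not rescue three unrestricted statements that cover outcomes to which full masking cannot apply.

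Some stronger readings are tempting, and the documents do not support them:

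- A reader might infer that masking gives the questionnaires no protection at all. Masked administration and scoring still guards against prompting, interpretation and scoring by staff who know the allocation.
- A reader might infer that the assessor-blinded label in the Design section is false. As a description of the staff assessors it is acceptable.
- A reader might infer that the diaries will unblind the assessor. The weekly sessions with the exercise physiologist or research nurse suggest that intervention staff may already handle them. The article simply leaves its general statement on blinded collection in conflict with that.
- A reader might infer that one-category shifts on five items show that expectation could explain the whole target. That only restates 5 points and is not an estimate of bias.

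Usual care as comparator, and support as part of the exercise package, are declared design choices and not errors.

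**Conclusion.** The point holds in a limited form. The Abstract, Randomisation and Data Collection sections attribute masked assessment to every outcome, but for the sole primary outcome and four of the six secondary domains the rating comes from participants who know their allocation (for medication, inpatient notes aside). For these outcomes, masking limits staff influence and does not blind the rating. Full assessor blinding holds only for the physical performance and body measurements.

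The outcome, sample size and analysis are not affected. What changes is what the primary result can be said to show. The direction and size of any expectation bias cannot be derived from the documents.

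The conclusion assumes that the IPAQ answers come from the participant, and that the unspecified clinician interviews do not yield the PCL-C score. The diary point is a precaution against an unclear procedure, not a demonstrated breach of masking.

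**What to change.** 1. In the Abstract, Randomisation and Data Collection sections, restrict the statement of masked assessment to the physical performance and body measurements.
2. Describe the PCL-C, DASS, IPAQ, sleep indices and medication diary as reports by unblinded participants, administered and scored by masked staff. Mention the inpatient notes separately. The Design label can stay.
3. State the primary conclusion as an effect on self-reported symptoms in unblinded participants.
4. State that intervention staff, not the blinded outcome assessor, collect and handle exercise diaries and step logs.

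The cost is a few sentences and one rule on data handling, which may already be practice. No added participants, staff or assessments are needed. The stated design will read less favourably than it does now.

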**Discussion:**

This study will determine the effect of an individualised and progressive exercise intervention on PTSD symptoms, depression and anxiety, mobility and strength, body composition, physical activity levels, sleep patterns and medication usage among people with a DSM-IV diagnosis of PTSD.

**Trial Registration:**

ACTRN12610000579099

## Background

Mental health consumers typically have poorer health outcomes than people of a comparable age without mental health issues and are more likely to have metabolic conditions such as diabetes, hypertension and hypercholesterolemia [1]. Regular exercise has been shown to positively impact upon factors contributing to the metabolic syndrome as well as improving depressive and anxiety related symptoms [2-4]. Despite these findings, and the potential 'double impact' that regular exercise may have on conditions such as PTSD, mental health consumers are less likely to embark on and adhere to a regular exercise program [5].

In order to maintain health and reduce the risk of chronic disease, the American College of Sports Medicine (ACSM) recommends adults perform moderately intense cardio-respiratory based physical activity for 30 minutes a day, five days a week, or alternatively perform vigorously intense cardio-respiratory based exercise 20 minutes a day, 3 days a week in addition to performing eight to 10 strength-training exercises, with eight to 12 repetitions of each exercise twice a week [2]. When prescribing exercise for mental health consumers such as those with PTSD, meeting the ACSM guidelines should be the ultimate aim. However ensuring engagement with the program regardless of how minimal it may be is likely to be rudimentary to its success, and can allow for progressions to be made as the participants become more confident and adherent to the program.

PTSD affects an estimated 5% of Australians, with hyperarousal, re-experiencing and avoidance the main symptom clusters [6]. Depression, anxiety, drug and alcohol addiction and sleep disturbance are common psychiatric comorbidities [6]. Treatment modalities include medications, cognitive behavioral therapy, psychodynamic psychotherapy, eye movement desensitization and reprocessing (EMDR) and group psychotherapy. Evidence-based treatment for PTSD is still quite limited and there is no definitive evidence to guide pharmacological prescription. The International Consensus Group on Depression and Anxiety recommends selective serotonin reuptake inhibitors (SSRIs) and exposure therapy [6]. The 2007 Australian Guidelines for the Treatment of Adults with Acute Stress Disorder and Post Traumatic Stress Disorder state that exercise may be helpful in managing symptoms and as part of self-care more generally [7], but the clinical guidelines note that no studies have examined the effectiveness of exercise as an adjunct to other PTSD treatments.

At the time of writing, no randomised controlled trial (RCTs) had been conducted investigating the effects of an individualized and structured exercise program on patients with a DSM-IV diagnosis of PTSD [7,8]. A 2010 Cochrane Collaboration review titled 'Sports and games for post-traumatic stress disorder found that no RCTs had been conducted to assess the effect of sports or game based interventions on symptoms of PTSD [8]. Although the review identified five studies, none met the inclusion criteria as they were not randomised controlled trials [9], participants were not diagnosed with PTSD or a psychological based intervention was tested such as play-therapy [10,11].

Some evidence of the potential benefit of exercise on PTSD symptoms comes from a 2008 study by Diaz and Motta [12]. They conducted a non-randomised study involving twelve female adolescents diagnosed with PTSD. Their results showed that 91% of participants showed a significant reduction in PTSD symptoms on the Childhood PTSD Symptom Scale, following participation in a walking program [12]. The study had a number of limitations including the use of a low intensity exercise protocol which did not include progressive overload training, and failed to incorporate any of the ACSM guidelines regarding exercise prescription. Given the potential impact on both the PTSD symptoms and physical co-morbidities, there is a compelling need for an evidence-based approach to prescribing exercise for people diagnosed with PTSD.

The current RCT will investigate the effects of structured, progressive exercise on PTSD symptoms, depression and anxiety, mobility and strength, body composition, physical activity levels, sleep patterns and medication usage among people with a DSM-IV diagnosis of PTSD.

## Methods/design

### Design

An assessor-blinded RCT will be conducted. A total of 40 participants in each group (n = 80) will be recruited. The study will have 80% power to detect as significant at the 5% level a 5 point between group difference on the PCL-C (SD = 9.4) [13] allowing 15% dropouts. The study protocol has been designed and will be reported, with reference to the CONSORT Statement [14]. Figure 1 gives an overview of the study design.

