### Statistical analysis

Regression models will be used to assess the effect of group allocation on the primary and secondary outcome measures after adjusting for baseline values. An intention-to-treat approach will be used for primary analyses. A secondary per-protocol analysis will be conducted excluding people who do not comply with the intervention, defined as performing less than 30% of the recommended exercise sessions. A further secondary analysis will assess whether there is an interaction between baseline physical activity levels and group allocation. Analyses will be conducted using the SPSS and Stata software packages.

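### The stated 80% power cannot be reproduced from the inputs printed with it: they give about 58% unadjusted, and reaching 80% needs an assumption the protocol does not state

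*Protocol article*

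**What the plan says.** The protocol article justifies its sample size once, under Design. It sets recruitment there: "A total of 40 participants in each group (n = 80) will be recruited". It then claims "80% power to detect as significant at the 5% level a 5 point between group difference on the PCL-C (SD = 9.4"), "allowing 15% dropouts". The SD is taken from a cited source. The section does not name the test, whether it is one- or two-sided, or whether 9.4 is the SD of scores at one time point, of change, or of residuals after adjustment. It mentions no correlation between baseline and follow-up.

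The Statistical analysis section fixes the model: "Regression models will be used to assess the effect of group allocation on the primary and secondary outcome measures after adjusting for baseline values". Nothing links the power claim under Design to that adjustment.

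**The concern.** The power statement looks complete: difference, SD, significance level, group size and dropout stand together with the power they are said to give. A reader can therefore check it, and the check fails. A standardised difference of 5/9.4 = 0.53 with 34 completers per group falls well short of 80% in a simple comparison of means.

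This is the only sample-size justification, and it concerns the primary outcome. The stated power tells readers how often a true 5-point benefit would be detected, and so how much weight a non-significant result can bear. If the 80% depends on an undisclosed assumption, readers cannot judge whether that assumption is reasonable. If it depends on none, the figure is wrong.

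**Working it through.** **Inputs from the Design section.** Difference 5 points; SD 9.4; 5% level; 40 per group; 15% dropout, so 40 × 0.85 = 34 completers per group. Two-sided testing is my assumption, and one-sided results are shown as well.

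**Attempt to reproduce the 80%, unadjusted comparison.**

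Standard error of the difference = SD × √(2/n) = 9.4 × √(2/34) = 2.28. Non-centrality = 5/2.28 = 2.19. Power comes from the noncentral t distribution on 2n − 2 degrees of freedom.

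| Completers per group | Sides | Power (t) | Power (normal approx.) |
|---|---|---|---|
| 34 | two | 58.0% | 59.2% |
| 40 (no dropout) | two | 65.2% | 66.2% |
| 34 | one | 70.0% | 70.8% |
| 40 (no dropout) | one | 76.2% | 76.9% |

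No row reaches 80%, so neither sidedness, nor ignoring dropout, nor rounding explains the claim.

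**Size of the gap on the unadjusted reading.**

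- The difference detectable with 80% power at 34 per group is 6.5 points (6.48 by t; 6.4 by normal approximation).
- The completers needed for 80% power at 5 points by normal approximation are 2 × (9.4 × (1.96 + 0.84)/5)² ≈ 55.5, so 56 per group; the t-test needs 57. Dividing by 0.85 gives 66 or 68 recruited per group (132 or 136 in total), against 40 per group (80) planned.

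**Planned baseline-adjusted regression, 34 per group, two-sided.** The correlation r between baseline and 12-week scores is an assumption throughout, because the article gives none. The residual SD that yields 80% power is 7.25 (7.36 by normal approximation).

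*If 9.4 is a raw SD*, the residual SD is 9.4 × √(1 − r²):

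| r | Residual SD | Power (t) |
|---|---|---|
| 0.4 | 8.62 | 65% |
| 0.5 | 8.14 | 70% |
| 0.6 | 7.52 | 77% |
| 0.64 | 7.22 | 80% |
| 0.7 | 6.71 | 86% |

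Solving for 80%: r = √(1 − (7.25/9.4)²) = 0.64 (0.62 by normal approximation).

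*If 9.4 is the SD of change*, the raw SD is 9.4/√(2(1 − r)), and the residual SD is 9.4 × √((1 + r)/2):

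| r | Residual SD | Power (t) |
|---|---|---|
| 0.2 | 7.28 | about 80% |
| 0.5 | 8.14 | 70% |
| 0.7 | 8.67 | 65% |

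On this reading a higher correlation lowers power.

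*If 9.4 is already a residual SD*, adjustment brings nothing further and power stays at about 58%.

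**The case against.** The strongest reply is that 58% belongs to a test the trial does not plan to use. The Statistical analysis section commits to adjustment for baseline. With 9.4 as a raw SD, the adjusted analysis falls short by about 10 percentage points at r = 0.5 and 3 at r = 0.6, and not at all at r = 0.64. The authors may have counted on such a gain, and a condensed article may leave the assumed correlation to a fuller document.

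Much of this stands. A reader might infer that the trial is underpowered, that its power is 58%, or that a true 5-point benefit would be missed about four times in ten. The documents do not support that. Those figures describe an unadjusted analysis, or an adjusted one in which baseline explains nothing or 9.4 is already a residual SD. The article no more establishes those conditions than it establishes r = 0.64. Nor does it say that a null result would be taken to exclude a 5-point effect.

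The reply does not rescue the statement itself. The complaint is not that a detail was omitted: the figures printed together do not yield the power printed with them. Crediting the adjustment requires a particular reading of the SD together with a particular range of correlation, and the article gives neither.

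**Conclusion.** The power statement is wrong as written. On its printed inputs the power is about 58% (two-sided, unadjusted, 34 completers per group), and the most generous variant gives 76%. This part is firm and rests only on the article's own numbers.

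What cannot be concluded is the trial's true power. Under the planned adjusted analysis it could be anywhere from about 58% to above 80%, depending on what the 9.4 measures and on the correlation. The 80% is attainable if 9.4 is a raw SD and r is about 0.64 or more, or if 9.4 is an SD of change and r is about 0.2 or less. The defect therefore lies in the sample-size statement; it is not a demonstrated lack of power in the design.

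**What to change.** Correct the power sentence under Design, keeping n = 80, in one of two ways.

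1. If the 80% was calculated for the baseline-adjusted analysis, say so: two-sided 5% level, 34 completers per group, 9.4 as the raw SD, and an assumed baseline-to-12-week correlation of at least about 0.64. If the calculation used another kind of SD, give that and the correlation that goes with it.
2. If it was not, replace the 80% with what the inputs support: 34 completers per group give about 58% power for 5 points in an unadjusted two-sided comparison, with about 6.5 points detectable at 80% power. Label this clearly as unadjusted, and set beside it the power of the planned adjusted analysis over a range such as r = 0.4 to 0.7 (65% to 86% if 9.4 is a raw SD).

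The cost is one or two sentences, and under the second option a less favourable headline figure. No extra participants and no change to the design or the analysis are needed.
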